## **RISKS**

Some participants may experience some discomfort from having the blood samples collected and there may be some bruising that will resolve usually within a few days. The risks to the participant will be minimised by having this procedure performed by suitably trained members of staff. We are not aware of any risks of echocardiography.

The echocardiography and blood samples (soon after recruitment) and blood samples (around the 12 month follow-up) will require an additional two face-to-face visits for participants. Appropriate COVID-19 precautions will be taken (PPE, social distancing, hand hygiene).

## **ETHICAL CONSIDERATIONS**

In the BICS participant information sheet potential participants will be made aware that they might be approached for a further study, written informed consent will be obtained for this.

Participants will be approached to take part in the sub-study during the dose titration phase by a member of the BICS local study team and provided with a sub-study participant information sheet. Participants will be invited to take part in the BICS sub-study after they have agreed to take part in the main BICS study. Research nurses will be allowed discretion as to the exact timing of the approach which may be during their BICS recruitment visit or during the titration period. Participants expressing an interest (during ensuing week or at subsequent assessment) will be invited to provide written informed consent. If participants wish to give consent at the time they are provided with information about the sub-study, they can provide written informed consent at that time if they have read the information. The same arrangements for patients who cannot read and/or write as described in section 7.2 will apply to the cardiac sub-study.

Participants will be made aware that their blood samples will be sent to Edinburgh/Dundee for analysis. With consent, surplus samples will be stored.

The echocardiogram and blood tests (NT-proBNP, hs-TNI hs-CRP and Galectin) are not part of the routine care of people with COPD. To preserve the pragmatic nature of the BICS trial and to prevent the introduction of bias, all samples/images will be analysed a minimum of 12 months after randomisation when the participant has ceased involvement in the trial. If an immediately life threatening abnormality is obvious to the echocardiographer this will be discussed on an individual basis with the study team. Participants will be informed of this in the participant information sheet. Relevant results from the echocardiography will be issued as clinical reports to the participant's GP and/or local cardiology team.

## **DATA COLLECTION**

Echocardiographic and blood data collected during the study will be stored in the main BICS study database.

## **PARTICIPANT WITHDRAWAL**

Participants who decline further contact within the main BICS study will not be contacted further about the sub-study. Participants who decline to attend follow-up appointments within the main BICS study will not be contacted further about the sub-study.

Participants who cease study medication, or who fix their dose on 0 tablets are eligible for, and may continue in the sub-study. For these participants, there is no change to the timing of the sub-study assessments.

## STATISTICS AND DATA ANALYSIS

### Sample size

The sample size of 1574 for BICS is based on a reported mean (SD) rate of exacerbation for patients with COPD with  $\geq 2$  exacerbations in the previous year of 2.22 (1.86) in the subsequent year. BICS will be able to detect a 15% reduction in COPD exacerbations with 90% power at 5% significance level. In a review of the literature, Rutten et al reported that the prevalence of left ventricular systolic dysfunction in people with COPD varies considerably, with the highest prevalence (46%) amongst those with an exacerbation.

Recruitment of 900 BICS participants to the cardiac sub-study will have 80% power at the 5% level of significance to detect the following differences in rate of exacerbation in bisoprolol and placebo arms depending on the proportion of participants with occult heart disease. The power calculations factor in 10% of participants stopping study medication.

| % high risk occult heart disease | Exacerbation rate: placebo arm | Exacerbation rate: bisoprolol arm | Absolute difference exacerbation rate: bisoprolol vs placebo | % difference in exacerbation rate: bisoprolol vs placebo |
|----------------------------------|--------------------------------|-----------------------------------|--------------------------------------------------------------|----------------------------------------------------------|
| 50%                              | 2.22                           | 1.70                              | 0.52                                                         | 23%                                                      |
| 40%                              | 2.22                           | 1.64                              | 0.58                                                         | 26%                                                      |
| 30%                              | 2.22                           | 1.55                              | 0.67                                                         | 30%                                                      |
| 20%                              | 2.22                           | 1.40                              | 0.82                                                         | 37%                                                      |

The two possible extreme situations are that the sub-study:

- Will have 80% power at the 5% level of significance to detect a 23% reduction in the rate of exacerbation (2.22/yr vs 1.70/yr) if 50% of participants have occult heart disease.
- Will have 80% power at the 5% level of significance to detect a 37% reduction in the rate of exacerbation with bisoprolol (2.22/yr vs 1.40/yr) if only 20% of participants have occult heart disease.

The systematic review of Du et al reported that the observational studies of beta blockers in people with COPD is associated with a 37% reduction in exacerbations (95%CI 29-43%).

## PROPOSED ANALYSES

Predefined cutoffs will be used to risk stratify sub-study participants for occult, previously undiagnosed heart disease:

Hs TnI levels will be analysed using cutoffs that we have shown to be highly predictive in detecting subjects at high risk of silent cardiac target organ damage.

Pre-determined imaging cut-offs for in defining "occult, previously undiagnosed heart disease:

- Echo bi-plane LV EF<40% with dilated or non-dilated LV.
- Heart failure with mid-range EF (40-49%) for as per most recent ESC guidelines
- Heart failure with preserved EF ( $\geq 50\%$ ) who additionally have, as per ESC guidelines:
  - either NT-proBNP $\geq 125$  pg/ml
  - or with evidence of diastolic dysfunction (defined as abnormal LV relaxation by Doppler imaging, ie E/E' $>13$  or echo-enhanced left atrial volume $>34$  ml/m^2 or left ventricular hypertrophy diagnosed as LV mass index  $\geq 115$  g/m^2 for males and  $\geq 95$  g/m^2 for females. If current guidelines are superseded during the course of the study, the diagnostic criteria described in these will be used.

Statistical analyses will be according to the intention to treat principle. The primary outcome of number of COPD exacerbations requiring antibiotics and/or oral corticosteroids in the 12 month study period will be compared between randomised groups overall and in each subgroup (high and low risk occult heart disease) using negative binominal regression with length of time in study as an offset. To assess which biomarkers, their optimal cut-offs and/or which imaging outcome is the best method of identifying those most likely to benefit we will use ROC analysis along with sensitivity and specificity of the specific biomarker and imaging outcomes in identifying those which will show benefit. Benefit will be defined as no exacerbations during follow-up. We may

use logistic regression to assess which biomarkers/imaging measurements are best predictive alone or in combination of a beneficial outcome in terms of a reduction in COPD exacerbations.

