| Number of participants | 1,574 participants. More than 50% to be recruited from primary care.                                                                                                                                                                                                                                                                                                                                                                                                                                                                                                                                                                                                                                                                                                                                                                                                                                                                                                                                       |
| Eligibility criteria   | Inclusion criteria: 
 
• Aged <math>\geq 40</math> years.
 
• A smoking history of at least 10 pack years ([average number of cigarettes/day x years smoked]/20).
 
• An established diagnosis of COPD (NICE Guideline definition: post bronchodilator <math>FEV_1 < 80\%</math> predicted, <math>FEV_1/FVC < 0.7</math>) receiving treatment as per local guidelines'. During the COVID-19 pandemic, this will be based on historic evidence of <math>FEV_1 < 80\%</math> predicted, <math>FEV_1/FVC < 0.7</math>.
 
• A history of at least two exacerbations requiring treatment with antibiotics and/or oral corticosteroid use in the previous year, based on patient report OR a history of at least two exacerbations within 12 months of each other requiring treatment with antibiotics and/or oral corticosteroid since March 2019.
 
• Clinically stable with no COPD exacerbation for at least 4 weeks.
 
 |

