| Statistical methods        | 
Baseline characteristics will be described for both treatment groups. The primary outcome of number of COPD exacerbations will be compared between randomised groups using negative binomial regression with length of time in the study as an offset. Estimates will then be adjusted for centre and other baseline covariates that are known to be strongly related to the outcome. Sub-group analysis of participants with clinically diagnosed heart disease to determine whether any beneficial effects of bisoprolol are limited to those with clinically diagnosed heart disease.
                                                                                                                                                                                                                                                                                                                                                                                                                                                                                                                                                                                                                                                                                                                                                                                                                                                                                                                                                              |

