| Sub-study sample size estimate | BICS participants enrolled in secondary care sites will be invited to participate. We envisage about 900 participants.                                                                                                                                                                                                                                                                                                                                                                                                                                                                                                                                                                                                                                                                                                                                                                                                                                                                                                                                                                                                                                                                                                                                                                                                                                                                                                                                                                                                                                                                                                                                                                                           |

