## SUB-STUDY OBJECTIVES

### Primary Objective

To determine if any clinical success of beta-blocker therapy in COPD patients is restricted to those COPD patients at high risk of occult undiagnosed heart disease.

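### Cardiac sub-study (Appendix 6): the objective asks whether benefit is restricted to high-risk patients, but the stated analysis and the power table address separate subgroup comparisons, not the treatment-by-subgroup interaction

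*Protocol*

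**What the plan says.** Appendix 6, Primary Objective, asks whether any clinical success of beta-blocker therapy "is restricted to those COPD patients at high risk of occult undiagnosed heart disease".

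Appendix 6, Proposed Analyses, says the primary outcome will be "compared between randomised groups overall and in each subgroup (high and low risk occult heart disease) using negative binominal regression", with time in study as an offset. No treatment-by-subgroup interaction is named there or elsewhere in the protocol. The only interaction mentioned is treatment by time, for the repeated measures in section 10.3.

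Appendix 6, Sample size, says: "Recruitment of 900 BICS participants to the cardiac sub-study will have 80% power at the 5% level of significance". It tabulates detectable differences between bisoprolol and placebo of 0.52, 0.58, 0.67 and 0.82 exacerbations per year (23, 26, 30 and 37% of 2.22) for 50, 40, 30 and 20% of participants at high risk. It adds: "The power calculations factor in 10% of participants stopping study medication".

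Two inputs sit beside different figures in the main protocol. Section 10.1 allows for 15% withdrawal from study treatment. The Appendix 6 synopsis says "BICS participants enrolled in secondary care sites will be invited to participate. We envisage about 900 participants", while the main synopsis says of the 1,574: "More than 50% to be recruited from primary care".

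**The concern.** Saying that benefit is confined to one group means that the effect there differs from the effect in the other group. A significant result in high-risk patients does not show this, because a benefit shared by everyone would produce it too. A non-significant result in low-risk patients does not show absence of benefit. The direct test is the treatment-by-subgroup interaction.

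Appendix 6 carries its own objective, sample size and proposed analyses. Its abstract says the sub-study will establish whether therapy helps all patients or only those with occult heart disease, and its background asks whether treatment should be targeted. The stated analysis does not test that, and the stated 80% power belongs to a different comparison.

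**Working it through.** **Inputs.** Appendix 6, Sample size: 900 participants, 10% stopping, placebo mean (SD) 2.22 (1.86), 80% power, 5% significance. Section 10.3: two-sided. Section 7.3: equal allocation. Analysed number = 900 × 0.90 = 810. Per arm, n_high = 810 × share / 2 = 202.5, 162, 121.5, 81, and n_low = 405 − n_high = 202.5, 243, 283.5, 324.

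**1. Reproduce the table.** Compare two means inside the high-risk subgroup: detectable difference = (1.96 + 0.8416) × 1.86 × √(2/n_high). At 50%: 5.211 × √(2/202.5) = 0.518. The four rows give 0.518, 0.579, 0.669 and 0.819, matching 0.52, 0.58, 0.67 and 0.82. Low-risk patients do not enter the formula.

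**2. Interaction, comparison of means.** SE = 1.86 × √(2/n_high + 2/n_low). Assume the table's effect in high-risk patients and zero effect in low-risk patients. Power = Φ(difference/SE − 1.96); detectable interaction = 2.8016 × SE.

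**3. Interaction, negative binomial approximation.** Dispersion k = (1.86² − 2.22)/2.22² = 0.2515, one year of exposure. Variance of the log rate ratio is (1/2.22 + 1/μ_b + 2k)/n_high in the high-risk group, where μ_b is the tabulated bisoprolol rate, and (2/2.22 + 2k)/n_low in the low-risk group. At 50%: log effect 0.2669, SE √(0.0873² + 0.0833²) = 0.1206, ratio 2.21, power 60%.

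| High risk | Table difference | SE of interaction (means) | Interaction power, means | Interaction power, negative binomial | Interaction detectable at 80%, means |
|---|---|---|---|---|---|
| 50% | 0.52 | 0.2614 | 51% | 60% | 0.73 (33% of 2.22) |
| 40% | 0.58 | 0.2668 | 59% | 68% | 0.75 (34%) |
| 30% | 0.67 | 0.2852 | 65% | 76% | 0.80 (36%) |
| 20% | 0.82 | 0.3268 | 71% | 83% | 0.92 (41%) |

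Within-subgroup power under the negative binomial approximation is 86 to 90%, so the table is slightly conservative for the comparison it describes.

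**4. What separate p-values would show under a uniform effect.** Take the main trial's 15% reduction as true in both subgroups (rate ratio 0.85, log effect 0.1625), with 810 analysed. The variance is (1/2.22 + 1/1.887 + 2k)/n in each subgroup.

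| High risk | P(high-risk significant) | P(low-risk significant) | High-risk only | Exactly one |
|---|---|---|---|---|
| 50% | 0.48 | 0.48 | 25% | 50% |
| 40% | 0.40 | 0.55 | 18% | 51% |
| 30% | 0.31 | 0.61 | 12% | 54% |
| 20% | 0.22 | 0.67 | 7% | 59% |

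For example, at 20%: 0.224 × (1 − 0.671) = 7%. The comparison of means gives 25, 18, 12 and 8% for high-risk only.

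**5. The two inputs to reconcile.**
- With 15% stopping, 765 are analysed. Within-subgroup power at the tabulated differences becomes about 78%, roughly 2 points lower. Interaction power by means becomes 49, 56, 63 and 68%.
- More than half of 1,574 is at least 788, which leaves at most 786 for other settings, against about 900 planned.

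**The case against.** The strongest reply is that the table claims nothing false. It is labelled as a difference between bisoprolol and placebo arms, and its arithmetic is right. That stands. The fault is that it is the only power statement offered for an objective it does not address.

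Next, the appendix never says that restriction will be inferred from significance in one subgroup and not the other. Subgroup estimates are compatible with a later interaction test, and the Appendix 6 synopsis places the subgroups within the main analysis, so a SAP not seen here could supply one. This also stands. The misreading rates in step 4 are therefore conditional on a rule that the document does not state. The mismatch between objective and stated analysis remains.

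Third, the shortfall depends on the model. Under the negative binomial approximation the 20% row reaches 83%, above 80%. The other three rows fall short under either method.

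Three stronger readings are tempting but not supported:
- A reader might extend the criticism to the main trial's subgroup with clinically diagnosed heart disease, where the synopsis aims "to determine whether any beneficial effects of bisoprolol are limited to those with clinically diagnosed heart disease". The main protocol fixes no test there and leaves the detail to the SAP, so it states no wrong method.
- A reader might call 900 impossible given the primary care majority. Section 7.1 lets general practices act as identification centres for secondary care sites, and section 7.3 stratifies separately by centre and by where participants were identified. Patients found in primary care but enrolled at hospitals could reconcile the figures.
- A reader might treat 10% against 15% stopping as a serious contradiction. Sub-study assessments may come up to 12 weeks after randomisation, so a lower figure is arguable, although patients who have stopped remain eligible. The cost is about 2 power points.

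**Conclusion.** The point holds for Appendix 6. The sub-study's primary objective is a question about a difference between effects. The appendix specifies only comparisons overall and within subgroups, and its 80% power is for bisoprolol against placebo in high-risk patients.

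For the interaction at the tabulated effects, power is 51 to 71% by the table's own method and 60 to 83% under the negative binomial approximation. At 80% power the detectable difference between subgroup effects is 33 to 41% of the placebo rate. These figures assume zero effect in low-risk patients, the same placebo rate and dispersion in both subgroups, and patients who stop medication removed from the number analysed, as the table does.

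A false high-risk-only result under a uniform 15% effect would be fairly common at 50% high risk (25%) and uncommon at 20% (7%), and only if separate p-values were used as the rule. The main trial's primary analysis and sample size are not affected. The stopping rate and recruitment source are minor points to reconcile.

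**What to change.** In Appendix 6, Proposed Analyses, make the treatment-by-subgroup interaction in the negative binomial model the test of the sub-study primary objective. Report the rate ratio with its confidence interval in each subgroup as description. Carry the same wording into the SAP.

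In Appendix 6, Sample size, relabel the table as power within the high-risk subgroup and add interaction power, or the detectable interaction, for the same four shares, with the assumed low-risk effect stated.

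Reconcile 10% stopping with the 15% in section 10.1, or justify the difference. State how about 900 from secondary care sites fits with more than half of 1,574 from primary care, for example through general practices referring patients to hospital sites.

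The cost is wording and a less favourable power statement. No extra patients, visits or data are needed.

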### Secondary Objectives

To determine the best combination of biomarkers±echocardiography-derived parameters that reliably identifies the subgroup of COPD patients who will benefit from beta-blocker therapy for the purposes of COPD treatment.

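### The cardiac sub-study's marker search scores markers against freedom from exacerbations, which measures prognosis and not response to bisoprolol

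*Protocol*

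**What the plan says.** In Appendix 6, Secondary Objectives, the aim is to find the combination of biomarkers and echocardiographic parameters that "reliably identifies the subgroup of COPD patients who will benefit from beta-blocker therapy for the purposes of COPD treatment".

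Under Proposed Analyses the method for choosing markers and their cut-offs is: "we will use ROC analysis along with sensitivity and specificity of the specific biomarker and imaging outcomes in identifying those which will show benefit". The outcome for that step is then fixed: "Benefit will be defined as no exacerbations during follow-up". The appendix adds that the team may "use logistic regression to assess which biomarkers/imaging measurements are best predictive alone or in combination of a beneficial outcome". None of these sentences mentions allocated arm, a comparison with placebo, or a marker-by-treatment interaction.

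The same section handles the sub-study's primary objective separately. Predefined cut-offs sort participants into high and low risk of occult heart disease. The randomised arms are then compared overall and within each stratum by negative binomial regression with time in study as an offset.

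**The concern.** Benefit from a drug is a contrast between what happens with it and what would have happened without it. Having no exacerbations is a raw outcome, and placebo patients reach it too. Sensitivity, specificity and AUC against that outcome show how well a marker separates patients who stay event-free from those who do not, whatever the reason. A marker of milder disease does well even if bisoprolol works equally, or not at all, at every level of it. A marker of true response does badly if it also marks higher risk.

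The definition also drops follow-up time. The main analysis uses an offset because some participants withdraw early or die (Protocol, section 10.3). Under the 'benefit' rule, someone lost early with no recorded event counts as a success.

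At stake is the answer to the secondary objective. The Background of Appendix 6 asks whether treatment should be targeted at an identifiable sub-group. A cut-off found this way could favour patients with good prognosis and pass over the cardiac marker being sought.

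**Working it through.** **Inputs from the protocol.** Placebo mean and SD: "exacerbations in the previous year of 2.22 (1.86) in the subsequent year" (Appendix 6, Sample size; same figures in section 10.1). Target rate 1.89 (section 10.1). Sub-study: 900 participants, 10% stopping medication, 80% power at 5%, with 2.22 v 1.70 if 50% are high risk and 2.22 v 1.40 if 20% are. Allocation is 1:1 (section 7.3).

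**1. The plan's own power figures reproduce.** Evaluable high-risk participants per arm = 900 × 0.9 × prevalence / 2. SE = 1.86 × √(2/n). I take the 5% level as two-sided, as in the main trial.

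- 50%: n = 202.5, SE = 0.185, 0.52/0.185 − 1.96 = 0.85, power 80.3%.
- 20%: n = 81, SE = 0.292, 0.82/0.292 − 1.96 = 0.85, power 80.1%.
- The 40% and 30% rows give 80.1% and 80.2%.

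The fault is in the definition, not in the arithmetic.

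**2. How many placebo patients 'benefit'.** Matching a negative binomial to mean and SD: k = (1.86² − 2.22)/2.22² = 0.2515, and P(0) = (1 + kμ)^(−1/k).

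| Mean per year | P(no exacerbation) |
|---|---|
| 2.22 | 17.1% |
| 1.89 | 21.3% |
| 1.70 | 24.3% |
| 1.40 | 30.1% |

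At the target effect, 17.1/21.3 = 0.80. About 80% of the expected number of event-free bisoprolol patients would be expected on placebo anyway. In the sub-study scenarios, with the effect confined to marker-positives, 20.7% or 19.7% of the bisoprolol arm is event-free, and the share is 83% or 87%.

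Follow-up: at 2.22 per year the six-month mean is 1.11, so P(0) = 38%, against 17% at one year.

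**3. Score of an ideal response marker.** Take a binary marker with all of the treatment effect in marker-positives, equal prognosis, and both arms pooled. For a binary marker, AUC = (sensitivity + specificity)/2.

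- 50% positive: P(0) in positives = (17.1 + 24.3)/2 = 20.7%; in negatives 17.1%; overall 18.9%. Sensitivity = 0.5 × 20.7/18.9 = 0.547. Specificity = 0.5 × 82.9/81.1 = 0.511. AUC = 0.529.
- 20% positive: P(0) in positives = (17.1 + 30.1)/2 = 23.6%; overall 18.4%. Sensitivity = 0.256, specificity = 0.813, AUC = 0.535.

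**4. The same marker when positives have a higher underlying rate.** The ratio is an assumption, because the documents give no exacerbation rate by cardiac status. The overall placebo mean is held at 2.22.

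| Rate ratio, positive v negative | Pooled AUC, 50% positive | Pooled AUC, 20% positive |
|---|---|---|
| 1.0 | 0.529 | 0.535 |
| 1.1 | 0.509 | 0.521 |
| 1.2 | 0.491 | 0.509 |
| 1.3 | 0.475 | 0.498 |
| 1.6 | 0.432 | 0.473 |

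The AUC crosses 0.5 at about 1.15 in the first case and just under 1.3 in the second. At 1.3 with 50% positive, the event-free share in positives rises from 14.3% on placebo to 20.9% on bisoprolol, a real effect, while negatives stay at 20.7% in both arms. The pooled ROC still points the wrong way.

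**5. A marker with no interaction but better prognosis.** With 50% positive and an assumed rate ratio of 0.77 to 0.6, AUC is 0.556 to 0.605.

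**6. Using the bisoprolol arm alone.** This helps but does not cure the problem. With equal prognosis the ideal marker scores 0.554 (50% positive) or 0.566 (20% positive), close to the weaker prognostic marker in step 5. At a rate ratio of 1.3 with 50% positive it scores 0.501, and at 1.6 it scores 0.459.

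**The case against.** Four points on the other side deserve weight.

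- **Scope.** The step serves one secondary objective of an optional sub-study. The primary objective is answered by a randomised comparison within predefined strata that never uses the 'benefit' definition. This stands. A reader might infer that the sub-study's main result, or the trial's, is compromised; the documents do not support that.
- **Reversal is conditional.** With equal prognosis the true marker stays on the right side of 0.5. A reader might infer that the plan is bound to reject the right marker, or that any cut-off would select low-risk patients. That needs marker-positives to have a higher exacerbation rate, for which the documents give no figure. Section 2 of the protocol, which suggests that some apparent exacerbations may be cardiac events, makes the direction plausible but gives no size.
- **Size of the prognostic AUC.** It depends on the assumed strength of the marker, so only ranges for a like-for-like binary marker should be read from the working. On those, the prognostic marker's advantage is modest, and in the bisoprolol arm alone it can vanish.
- **The analysis plan could repair it.** The logistic regression is optional, and its wording speaks of a reduction in exacerbations, which hints at a comparison. But the protocol does not leave the outcome open. It states one, and that outcome does not match the objective. This is a choice stated wrongly, not detail deferred.

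**Conclusion.** Wrong as written, and worth correcting before analysis, though it is not a threat to the trial. The marker-selection step measures prognosis where the objective asks about response. That conclusion rests on the definitions alone and needs no assumed figure.

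The sizes rest on a negative binomial matched to the stated mean and SD, one rate ratio applied at every baseline rate, and complete one-year follow-up. On that basis an ideal response marker would look almost uninformative (pooled AUC 0.529 to 0.535). It could fall below 0.5 under moderate assumed differences in underlying rate, while a purely prognostic marker could score 0.556 to 0.605. The 80% figure is a ratio of expected numbers; it does not say which individual patients would have been event-free on placebo.

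**What to change.** Delete the definition of benefit and its use as the ROC outcome. For each candidate marker, fit the planned negative binomial model with its time offset in both arms, adding the marker and its interaction with treatment. Rank markers by that interaction, and report the bisoprolol-to-placebo rate ratio across the marker range. Treat any cut-off derived from these data as exploratory. In the scenarios above this separates the two kinds of marker: rate ratios of 1.70/2.22 = 0.77 or 1.40/2.22 = 0.63 in positives against 1.00 in negatives for the true marker, and no interaction for the prognostic one.

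The cost is a change of wording and a little more analysis, with no new data or participants. The downside is precision. In the 50% scenario, with 202.5 evaluable per arm in each stratum, the SE of the log interaction is about √[(3 × (1/2.22 + 0.2515) + (1/1.70 + 0.2515))/202.5] = 0.12 against an effect of ln(0.77) = −0.27, or roughly 60% power. The report should say so.
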